The fieldworkers assessed anthropometric measurements, blood pressure, pulse rate, and peak expiratory flow rate on each participant at their home. Systolic and diastolic blood pressure and pulse measurements were taken 3 times with the patient seated and the left arm at the level of the heart after the participant was seated for 5 minutes. An Omron M1 electronic blood pressure manometer was used. In addition information on smoking status, diabetes status, medications for hypertension, and body-mass-index were collected and will be used in the calibration model. Population based means for these values with standard errors will be used to model death rates from CVD.

To assess calibration (the degree of similarity between observed and predicted risks) we will calculate the mean predicted risk of cardiovascular disease at 10 years and the observed risk at 5 years obtained using the 5 year Kaplan-Meier estimate. We then compared the ratio of the predicted to the observed cardiovascular disease risk for patients in the validation cohort in each tenth of predicted risk.

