**Risk Prediction Validation**

The calibration of the CVD risk score is important for national projections of disease incident and projections of future mortality based on changes in the various risk factors. However, for its reliable use in predicting individual risk, validation in prospective cohorts is ideal. CVD prediction charts for the different regions of the world that do not require lab testing have been suggested (Mendis *et al*, 2007; Lim *et al*, 2007) by the WHO but they have never been compared with any of the standard risk prediction rules or validated in any cohort. We will attempt to validate both the non-lab based prediction tool from our work in the NHEFS cohort as well as the WHO risk prediction charts.

To develop and validate a new score we will use the cohort of approximately 2000 patients described in the main programmatic trial outline below in a separate protocol who are over the age of 35 and without prior history of CVD. Our endpoint for censoring as described will be all cause mortality and CVD mortality encompassing the appropriated ICD codes for ischemic heart disease, stroke and hypertensive heart disease. Participants will also be asked to provide their South African identity number. This will be used to link with the national mortality register at 5 and 10 years from the start of the study. Unfortunately, data collection methods and resources do not allow for us to confirm non-fatal CVD events. We hope to eventually use this pilot data for use in a larger cohort to evaluate both morbidity and mortality data for a more refined risk scoring mechanism.

Therefore we propose to use the information from the cohort of patients enrolled in the cluster randomized control trial (described below) to validate the risk score. The initial evaluation will allow us to develop a risk score for total mortality. In the NHEFS cohort above, a risk prediction tool using non-lab based values had remarkable discrimination in predicting those at high risk for overall mortality with a C-statistic of 0.85 and 0.86 for women and men respectively. We will then test for predictive accuracy in predicting CVD mortality even though we recognize that there is likely to be some misclassification due to the incomplete death certification in South Africa.

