We included the following risk factors in our analysis to compare a lab-based tool to a non-lab based tool, using the value closest to the entry date to the cohort for each patient: age (in single years); gender (men v women); smoking status (current smoker, non-smoker—including former smoker); systolic blood pressure (continuous); ratio of low density lipoprotein cholesterol to high density lipoprotein levels (continuous); body mass index (continuous); current prescription of at least one antihypertensive (yes or no), and diabetes status (yes or no). Having calibrated the model from the national data we can then apply this data from this specific validation cohort. We calculated the 5 year estimated cardiovascular disease risk for each patient in the validation dataset. For development and validation of the new risk score we will use Cox proportional hazards regression to assess the “lab-based” model and compare it with the “non lab-based” model.

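### Calibration scored as predicted over observed CVD risk by tenth has no value in a tenth without a CVD death, which is likely in the low-risk tenths unless CVD mortality is high

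*Combined protocol and SAP*

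**What the plan says.** The measure is set out under Proposed Model Calibration Approach. Predicted risk comes first: "we will calculate the mean predicted risk of cardiovascular disease at 10 years". Against it stands "the observed risk at 5 years obtained using the 5 year Kaplan-Meier estimate". The comparison is "the ratio of the predicted to the observed cardiovascular disease risk for patients in the validation cohort in each tenth of predicted risk". Observed risk is therefore the denominator, tenth by tenth.

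Risk Prediction Validation describes "the cohort of approximately 2000 patients" "who are over the age of 35 and without prior history of CVD". The endpoints are "all cause mortality and CVD mortality encompassing the appropriated ICD codes for ischemic heart disease, stroke and hypertensive heart disease", obtained by linkage to the mortality register at 5 and 10 years. It adds that "data collection methods and resources do not allow for us to confirm non-fatal CVD events". Later in that section the prediction horizon is 5 years: "We calculated the 5 year estimated cardiovascular disease risk for each patient in the validation dataset".

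The protocol gives no CVD death rate or expected number of deaths for this cohort. It has no rule for a tenth without events, no interval for the ratio and no second calibration measure.

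**The concern.** The Kaplan-Meier risk in a tenth with no CVD death by 5 years is zero, so predicted over observed does not exist there. With one or two deaths it exists but is fragile: going from one death to two halves it.

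A tool that discriminates well pushes deaths into the top tenths and empties the bottom ones, so the measure loses more tenths for the better tool. The protocol intends to assess the non-laboratory score, the WHO charts, and laboratory against non-laboratory models. If each is scored this way, they could be judged on different subsets of tenths. With no rule for an empty tenth, the analyst has to decide after seeing the data whether to drop or merge it, and that choice changes the picture of calibration.

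**Working it through.** The plan has no figure to reproduce, so this is a conditional calculation.

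**Inputs from the protocol**
- About 2000 patients in tenths, so 2000 / 10 = 200 per tenth.
- Observed event: CVD death by 5 years.
- C-statistic 0.831 for the non-laboratory model (Background and Significance of the validation study: women, US cohort, fatal and non-fatal first events), and 0.85 to 0.86 for overall mortality (Risk Prediction Validation).

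**Assumptions**
- Five-year CVD mortality of 1% to 10%.
- C = 0.83 or 0.855 carries over to CVD death in this cohort; 0.75 and 0.70 are weaker alternatives.
- The tool is perfectly calibrated on a 5-year CVD-death scale, and follow-up to 5 years is complete.
- The linear predictor is normal and risk is logistic, scaled to the chosen C and overall rate.

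**Formulas**, with p_j the mean risk in tenth j:
- P(no death in tenth j) = (1 − p_j)^200
- P(at least one undefined ratio) = 1 − Π[1 − (1 − p_j)^200]
- Mean number of undefined tenths = Σ(1 − p_j)^200

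**Worked case: 2% mortality (2000 × 0.02 = 40 deaths), C = 0.83**

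| Tenth | 1 | 2 | 3 | 4 | 5 | 6 | 7 | 8 | 9 | 10 |
|---|---|---|---|---|---|---|---|---|---|---|
| Expected deaths | 0.17 | 0.40 | 0.66 | 0.98 | 1.41 | 2.00 | 2.86 | 4.27 | 7.08 | 20.2 |
| P(no death) | 0.847 | 0.671 | 0.517 | 0.373 | 0.243 | 0.134 | 0.056 | 0.013 | 0.001 | 0.000 |

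P(at least one undefined) = 1 − (0.153 × 0.329 × 0.483 × 0.627 × 0.757 × 0.866 × 0.944 × 0.987 × 0.999) = 0.991. The P(no death) row sums to about 2.85 undefined tenths.

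**Across the assumed range: chance of at least one undefined tenth**

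| 5-year CVD mortality | 1% | 2% | 3% | 5% | 10% |
|---|---|---|---|---|---|
| C = 0.855 | >99% | >99% | 99% | 94% | 71% |
| C = 0.83 | >99% | 99% | 96% | 84% | 50% |
| C = 0.75 | 99% | 87% | 67% | 35% | 6% |
| C = 0.70 | 97% | 70% | 42% | 13% | 1% |

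At C = 0.83 the mean number of undefined tenths is 4.35, 2.85, 2.09, 1.30 and 0.55. Other ways of turning C = 0.83 into a spread of risk give somewhat lower chances, down to 76% at 5% and 33% at 10%.

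**Better tools lose more.** At 2% mortality the mean number of undefined tenths is 1.6 at C = 0.75, 2.85 at C = 0.83 and 3.4 at C = 0.855.

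**Effect of dropping empty tenths.** A tenth that is kept has at least one death, so its ratio cannot exceed its expected deaths divided by 1. In the worked case the lowest four tenths can then show at most about 0.17, 0.40, 0.66 and 0.98. A perfectly calibrated tool would look as if it under-predicts there.

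**Would fifths cure it?** Expected deaths by fifth in the worked case are 0.57, 1.64, 3.41, 7.13 and 27.2. Using e^(−expected), P(no death) is about 0.57, 0.19, 0.03, 0.001 and 0. P(at least one empty fifth) = 1 − (0.43 × 0.81 × 0.97 × 0.999) ≈ 0.66.

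**What zero deaths still tells us.** For 0 of 200 the exact 97.5% upper limit on risk is 1 − 0.025^(1/200) = 1.83%. Observed over expected is 0, with an exact Poisson upper limit of −ln(0.025) / 0.17 = 3.69 / 0.17 ≈ 22 in the lowest tenth. It is defined, but wide.

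**The case against.** Several objections have force.

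- **The event rate is unknown.** A reader might infer that an undefined ratio is certain. The documents do not support that: at 10% mortality and C = 0.75 the chance is only about 6%. These are clinic attenders, many with treated hypertension or diabetes, so a higher rate cannot be excluded.
- **The C-statistic is borrowed.** The 0.83 is for women in a US cohort, with non-fatal events included. Its transfer to CVD death here is an assumption, and weaker discrimination softens the problem considerably.
- **The purpose is to find people at high risk.** A reader might infer that the measure fails where the tool is meant to rule people out. Section 3.4 and Background and Significance describe finding people at high risk and state no rule-out use or low-risk threshold. At C = 0.83 the top tenth expects about 10, 20, 30 and 47 deaths at 1%, 2%, 3% and 5% mortality, so the ratio is defined there. Nor does the middle of the range generally fail: the fifth tenth is empty with probability 0.24 at 2% and about 0.02 at 5%.
- **Merging is not dropping.** Merging loses nobody and leaves the pooled ratio at 1.00, though groups formed by merging an empty tenth upward tend to show apparent over-prediction (about 1.28 to 1.43 at C = 0.83 and 1% to 5% mortality). The under-prediction belongs to dropping only, and only where about one death or fewer is expected. The protocol proposes neither.
- **All-cause mortality and 10-year linkage are also planned** and would supply more deaths. The calibration rule, however, is written for cardiovascular risk at 5 years.
- **The calibration section does not define the validation cohort.** Taking it as the 2000 patients is the natural reading, not a stated one.

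These points limit the size and reach of the concern. They do not supply a rule for a zero denominator.

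**Conclusion.** The concern holds in conditional form. The stated ratio is undefined in any tenth without a CVD death and very unstable with one or two. At C = 0.83, at least one undefined tenth is at least 95% likely if 5-year CVD mortality is about 3.2% or less, and at least 50% likely up to about 9.9%. At C = 0.75 those limits fall to about 1.5% and 3.9%. The damage is in the lower tenths, grows with discrimination, and leaves the top tenth usable. This rests on the assumed death rate and C-statistic, on perfect calibration and complete follow-up, and on taking the 2000 patients as the validation cohort.

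Setting 10-year predicted risk against 5-year observed risk is a separate fault in the same paragraph. Putting both at 5 years would not remove the zero denominator.

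**What to change.** Under Proposed Model Calibration Approach, replace the per-tenth ratio with observed over expected CVD deaths, expected in the denominator, overall and in risk groups fixed in advance. Give exact intervals and keep groups with zero deaths. Put predicted risk and observed deaths on the same horizon and endpoint, and name the validation cohort. Add the calibration intercept and slope, which use all patients. State the expected number of CVD deaths with the rate assumed.

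Coarser groups are optional; as the fifths calculation shows, they do not solve the problem alone. The cost is a change of analysis wording and a little more analysis work, with no new data. The low-risk groups will show wide intervals, which is an honest statement of what about 200 people per group can tell.

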**Risk Prediction Validation**

The calibration of the CVD risk score is important for national projections of disease incident and projections of future mortality based on changes in the various risk factors. However, for its reliable use in predicting individual risk, validation in prospective cohorts is ideal. CVD prediction charts for the different regions of the world that do not require lab testing have been suggested (Mendis *et al*, 2007; Lim *et al*, 2007) by the WHO but they have never been compared with any of the standard risk prediction rules or validated in any cohort. We will attempt to validate both the non-lab based prediction tool from our work in the NHEFS cohort as well as the WHO risk prediction charts.

To develop and validate a new score we will use the cohort of approximately 2000 patients described in the main programmatic trial outline below in a separate protocol who are over the age of 35 and without prior history of CVD. Our endpoint for censoring as described will be all cause mortality and CVD mortality encompassing the appropriated ICD codes for ischemic heart disease, stroke and hypertensive heart disease. Participants will also be asked to provide their South African identity number. This will be used to link with the national mortality register at 5 and 10 years from the start of the study. Unfortunately, data collection methods and resources do not allow for us to confirm non-fatal CVD events. We hope to eventually use this pilot data for use in a larger cohort to evaluate both morbidity and mortality data for a more refined risk scoring mechanism.

Therefore we propose to use the information from the cohort of patients enrolled in the cluster randomized control trial (described below) to validate the risk score. The initial evaluation will allow us to develop a risk score for total mortality. In the NHEFS cohort above, a risk prediction tool using non-lab based values had remarkable discrimination in predicting those at high risk for overall mortality with a C-statistic of 0.85 and 0.86 for women and men respectively. We will then test for predictive accuracy in predicting CVD mortality even though we recognize that there is likely to be some misclassification due to the incomplete death certification in South Africa.

We included the following risk factors in our analysis to compare a lab-based tool to a non-lab based tool, using the value closest to the entry date to the cohort for each patient: age (in single years); gender (men v women); smoking status (current smoker, non-smoker—including former smoker); systolic blood pressure (continuous); ratio of low density lipoprotein cholesterol to high density lipoprotein levels (continuous); body mass index (continuous); current prescription of at least one antihypertensive (yes or no), and diabetes status (yes or no). Having calibrated the model from the national data we can then apply this data from this specific validation cohort. We calculated the 5 year estimated cardiovascular disease risk for each patient in the validation dataset. For development and validation of the new risk score we will use Cox proportional hazards regression to assess the “lab-based” model and compare it with the “non lab-based” model.

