Preliminary work in developed country cohorts has tested the hypothesis whether a non lab-based screening tool for cardiovascular disease could predict risk for CVD nearly as well as one that did require blood testing. We have found that in well characterized cohorts in the United States a simple screening tool that does not require lab testing can predict future CVD events as well as one that requires lab testing (Gaziano, 2008). This is important because a lack of financial, human and laboratory resources make lab testing impractical and costly in low resource settings. We compared two Cox models. The first is the “lab-based” model which requires blood testing and the second, which we designate as the “non lab-based” model, requires only history and physical exam measures. In both we compared how well either model could predict first time fatal and non-fatal CVD events in the NHANES I Epidemiologic Follow up Study (NHEFS) cohort. Both predictive models performed well in discriminating risk. In the women, the “lab-based” model performed well in predicting events with a C-statistic (95% confidence intervals) of 0.829 (0.813-0.845) The C-statistic of the “non lab-based” model was 0.831 (0.816-0.847). The test for significant difference between the two c-statistics is a chi-square result of 2.476 (p=0.116). Similar results were found for men. (Figure 2)

The next stage is to show that a screening mechanism using the same risk factors that does not require lab testing can also predict well in a different population. We also wish to test what is the most cost-effective and practical strategy for screening for CVD in South Africa. Therefore, the purpose of this proposal is continuing with the development of a simple risk prediction tool for CVD and to assess its cost-effectiveness in South Africa. Hopefully, the strategies can then be incorporated into national or international guidelines for the management of cardiovascular disease.

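### The new risk score is developed and validated in the same roughly 2000 patients with no optimism correction, so its reported performance will be apparent rather than validated

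*Combined protocol and SAP*

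**What the plan says.** The combined protocol and SAP covers this under Risk Prediction Validation. It opens the plan for the new score with "To develop and validate a new score we will use the cohort of approximately 2000 patients described in the main programmatic trial outline", restricted to those over 35 without prior cardiovascular disease. The next paragraph returns to the patients of the cluster trial for validation and adds "The initial evaluation will allow us to develop a risk score for total mortality"; cardiovascular mortality follows. The method is given once for both purposes: "For development and validation of the new risk score we will use Cox proportional hazards regression", comparing a lab-based with a non-lab-based model. Eight risk factors are listed. Deaths come from linkage to the national mortality register at 5 and 10 years. No expected number of deaths is given.

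Calibration is described under Proposed Model Calibration Approach as ratios of predicted to observed risk by tenth of predicted risk. The general Data analysis section refers back to the individual study sections for analysis plans, so the method is not set out elsewhere.

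A second strand in the same section applies existing scores to this cohort: the non-lab tool from the NHEFS cohort (the follow-up of the US NHANES I survey) and the WHO charts.

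**The concern.** A model assessed on the patients it was fitted to looks better than it will in new patients, because its coefficients have partly fitted the chance features of that sample. The C-statistic is inflated. The predicted-to-observed ratios by tenth are also drawn towards 1, so they cannot show that predictions are too extreme.

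According to the Synopsis, the non-laboratory tool goes into future versions of the guideline once validated. If the re-estimated score were called validated on these figures, clinicians would be given risks more spread out than the data support.

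**Working it through.** **Inputs from the documents.** About 2000 patients. Eight listed predictors: age, sex, smoking, systolic pressure, LDL/HDL ratio, body mass index, antihypertensive prescription and diabetes. NHEFS C-statistics for women are 0.829 (lab) and 0.831 (non-lab), with chi-square 2.476 and p = 0.116. NHEFS C-statistics for overall mortality are 0.85 (women) and 0.86 (men).

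**The plan's own figure.** The upper tail of chi-square 2.476 on 1 degree of freedom is 0.1156, which agrees with 0.116. The difference is 0.831 − 0.829 = 0.002, with implied standard error 0.002/√2.476 = 0.0013 (from rounded C-statistics).

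**Assumptions.** Deaths are 2%, 5%, 10% or 20% of 2000, that is 40, 100, 200 or 400. True C is about 0.86, 0.80 or 0.70. The split of predictors between models is not stated, so two versions were tried: seven terms each, with the lipid ratio replacing body mass index in the lab model; or nested, with seven terms and eight. Predictor distributions and effects are also assumed.

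**Method.** Cox models were fitted to simulated cohorts of 2000, censored at 5 years, with 250 to 300 replicates per scenario. C is the concordance of 5-year events against non-events, and optimism = apparent C − C in an independent sample.

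**Optimism in one C-statistic (non-lab model, seven terms)**

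| Deaths | C about 0.86 | C about 0.80 | C about 0.70 |
|---|---|---|---|
| 40 | 0.0210 | 0.0271 | 0.0496 |
| 100 | 0.0075 | 0.0110 | 0.0210 |
| 200 | 0.0041 | 0.0061 | 0.0106 |
| 400 | 0.0023 | 0.0027 | 0.0056 |

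Optimism falls roughly as one over the number of deaths. At C about 0.80, 0.0271 × 40 = 1.08, 0.0110 × 100 = 1.10 and 0.0027 × 400 = 1.08, so optimism is close to 1.1/deaths.

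A separate simulation with eight normal predictors and 57 assumed deaths gave an apparent C of 0.761 against 0.735 in new patients. The optimism of 0.026 lies between the values of 0.020 (C 0.80) and 0.033 (C 0.70) found at about 60 deaths. The calibration slope in new patients was 0.89 in that single scenario.

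**Optimism in the lab minus non-lab difference**

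- Seven terms each: within 0.0006 of zero at 100 or more deaths, and at most about 0.002 in size at 40 to 60 deaths.
- Nested, C 0.80 to 0.86: +0.0023 to +0.0032 at 40 deaths, +0.0012 to +0.0020 at 100, +0.0008 to +0.0012 at 200, and +0.0003 to +0.0004 at 400.
- Nested, C 0.70, 40 deaths: +0.0067, the extreme case.
- Sampling standard deviation of the observed difference with seven terms each: 0.002 to 0.009, usually larger than its optimism.

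**The case against.** The strongest reply is that most of what the plan calls validation is sound. The NHEFS tool and the WHO charts were built elsewhere. The NHEFS score is to be recalibrated on national survey and death data, and 5-year risk is then calculated for each cohort member. Those scores carry no overfitting from this cohort. A reader might infer from the shared cohort that the whole exercise is circular, or that no score with coefficients fixed in advance is tested. The text does not support that, and the point is confined to the new score.

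Second, total mortality is modelled first. With discrimination near the NHEFS values of 0.85 and 0.86 and several hundred deaths, the optimism is 0.002 to 0.004. That stands, although the plan gives no count to show that it is in this range. Cardiovascular mortality at 5 years will yield fewer deaths.

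Third, the authors call these pilot data for a hoped-for larger cohort and acknowledge misclassified causes of death. This lowers the stakes, but it does not replace an internal-validation step in an analysis described as validation.

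**Conclusion.** The point holds for the new score. As written, the plan would report apparent performance. Over 40 to 400 assumed deaths, the C-statistic is too high by about 0.05 down to 0.002. That is material when deaths are few and minor when there are several hundred. These figures rest on assumed death counts, discrimination and predictor effects. The fall with increasing deaths was seen at all three levels of discrimination.

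Two stronger readings are tempting and should not be drawn. The first sets this optimism against the NHEFS difference of 0.002 (0.002/0.002 = 1 to 0.05/0.002 = 25 times) and concludes that the choice between lab and non-lab models is swamped. Two models fitted to the same patients share most of their optimism, so it largely cancels in the difference, and sampling error is usually the larger threat. Moreover, 0.002 is an earlier result in women, not a margin or decision rule of this plan.

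The second is that clustering and trial arm make the Cox intervals too narrow by a known amount. The section is silent on both, but the documents give no intracluster correlation for mortality and no arm effect on it, so no size can be claimed.

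**What to change.** In Risk Prediction Validation:

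- Report the validation of the existing scores, fixed in advance of this cohort, separately from the development of the new score.
- For the new score, report a bootstrap optimism-corrected C-statistic and calibration. Resample whole clinics, repeat every step of the fitting in each resample, evaluate each refit in its resample and in the full cohort, and subtract the mean difference from the apparent value. Resampling clinics also carries the clustering into the results.
- Apply the resulting shrinkage to the coefficients before the score is released.
- Give the lab versus non-lab difference with a confidence interval from the same clinic-level bootstrap.
- State the expected number of deaths for each endpoint and horizon, so that readers can judge how much correction to expect.

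Stratifying the baseline hazard by trial arm is not proposed, because it would leave no single absolute risk for a screening tool to report.

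No new data are needed. The cost is some programming and a slightly lower reported C-statistic.

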**Recruitment, enrollment and data collection**

Trained fieldworkers will invite patients 18 years or older in the waiting room to participate in the study *after* their clinical consultation, and provide them with an information sheet, allowing them time to consider and discuss possible participation. Interested patients will be screened after consultation with the nurse/doctor, and in privacy, in an area of the clinic temporarily allocated to research staff.

Eligible participants who provide consent will be asked to undergo the following research procedures: measurement of their blood pressure, waist circumference, hip circumference, height, weight and an interview to determine: care received at the clinic, symptom severity, impact on their quality of life, healthcare utilisation, and the costs incurred by illness. Participants will also be asked to provide their South African identity number and any hospital folder numbers if available, to permit linkage with the national mortality register and hospitalisation databases respectively, thereby permitting long-term (5 years or more) follow-up.

In around 1/3 of participants, blood will be drawn to determine blood lipids (fats) and a marker of control of diabetes (HbA1C). Participants who qualified for the trial will be asked to return to the clinic 12-15 months later for a follow-up interview. An incentive to the value of R100 in the form of a voucher for a local grocery shop, will be provided to those participants who return for the follow-up interview. Participants who incur significant travel costs to return to the clinic for the follow-up interview will be reimbursed accordingly.

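### The calibration ratio for the existing risk tool does not restrict the prediction to fatal CVD, although the cohort's endpoints are deaths; one outcome and one horizon should be fixed for both sides.

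*Combined protocol and SAP*

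**What the plan says.** All of this is in the combined protocol and SAP, mainly in the chapter on the cardiovascular risk assessment tool.

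- **What the tool predicts.** Background and Significance describes the lab and non-lab models from NHEFS: "In both we compared how well either model could predict first time fatal and non-fatal CVD events". The Synopsis gives the tool's target as strokes, heart attacks and death.
- **What is to be validated.** Risk Prediction Validation: "We will attempt to validate both the non-lab based prediction tool from our work in the NHEFS cohort", together with the WHO charts.
- **What the cohort observes.** The same section: "Our endpoint for censoring as described will be all cause mortality and CVD mortality encompassing the appropriated ICD codes". It adds: "Unfortunately, data collection methods and resources do not allow for us to confirm non-fatal CVD events". The cohort is about 2000 people, with mortality linkage at 5 and 10 years.
- **How calibration is judged.** Proposed Model Calibration Approach: "We then compared the ratio of the predicted to the observed cardiovascular disease risk for patients in the validation cohort", by tenth of predicted risk. The sentence before it sets a mean prediction at 10 years beside a Kaplan-Meier estimate at 5 years. Risk Prediction Validation speaks instead of a five-year predicted CVD risk.
- **What the model is recalibrated to.** Proposed Model Calibration Approach gives three targets: observed South African mortality; rates of CVD illness as well as death (here naming the lab-based tool); and CVD death rates.

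**The concern.** A predicted-to-observed ratio can be interpreted only if both sides count the same thing over the same period. Here the existing tool counts fatal and non-fatal first events, while the observed side can count only deaths. The plan never says which outcome the prediction carries when it enters the ratio. If the existing tool is used as it stands, an accurate tool would appear to over-predict, and the size of that artefact would depend on a quantity the plan does not give. Matching the horizons does not remove it.

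This ratio is the only calibration measure named for the cohort, and calibrating and validating the tool is the stated purpose of this component. The Synopsis says the tool will enter future versions of the guideline once validated. The component's main absolute-risk result is therefore at stake.

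**Working it through.** The documents state no predicted-to-observed ratio and no fatal share of CVD events, so there is no figure of the plan's own to reproduce. The size has to be shown over an assumed range.

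**Inputs**
- Predicted outcome: fatal plus non-fatal first CVD events (Background and Significance).
- Observed outcome: CVD death (Risk Prediction Validation).
- Horizons: 5 v 5 years, to isolate the outcome mismatch; 10 v 5 years, as worded in Proposed Model Calibration Approach.
- Assumed: a tool exactly accurate for fatal plus non-fatal CVD; constant hazards; CVD deaths a share *f* of the total CVD hazard, with *f* from 0.7 to 0.2. Competing deaths are ignored.

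**Formulae**
- For ten-year predicted risk *R*, the total hazard is h = −ln(1 − R)/10.
- Ratio = [1 − exp(−h·Tp)] / [1 − exp(−h·f·To)], where Tp and To are the predicted and observed horizons.
- At low risk and equal horizons this is approximately 1/f.

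**Result for R = 10%.** h = −ln(0.9)/10 = 0.010536. The five-year predicted risk is 1 − exp(−0.05268) = 5.132%.

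| Assumed fatal share f | Observed 5-year CVD death | Ratio, 5 v 5 years | Ratio, 10 v 5 years |
|---|---|---|---|
| 0.7 | 3.620% | 1.42 | 2.76 |
| 0.6 | 3.111% | 1.65 | 3.21 |
| 0.5 | 2.600% | 1.97 | 3.85 |
| 0.4 | 2.085% | 2.46 | 4.80 |
| 0.3 | 1.568% | 3.27 | 6.38 |
| 0.2 | 1.048% | 4.90 | 9.54 |

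**Other risk levels.** At 5 v 5 years, f = 0.7 to 0.2 gives 1.42 to 4.95 when R = 5%, and 1.38 to 4.53 when R = 40%. The factor is therefore close to, but not exactly, constant across the tenths. If the fatal share itself varies with age, the ratio would vary across tenths for that reason too.

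**Horizon alone.** With outcomes matched (f = 1) and 10 v 5 years kept, the ratio for an accurate tool is 1.97 at R = 5% and 1.77 at R = 40%.

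**Death capture.** The protocol puts register completeness at more than 90%. At exactly 90%, the ratio rises by a further factor of about 1/0.9 = 1.11.

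**After the fix.** With outcome and horizon both matched and deaths fully captured, an accurate tool gives 1.0 by construction.

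**The case against.** The strongest reply is that a mortality prediction is what the investigators intend. The validation study is described as having a mortality outcome. The calibration section aims to fit model outputs to observed mortality and, shortly before the ratio, speaks of modelling CVD death rates. Risk Prediction Validation first develops a score for death from any cause, then tests it on CVD mortality, and applies the model to the cohort after national calibration. If the prediction has been re-anchored to CVD death by then, the mismatch disappears.

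This stands in part: the text is ambiguous, and it cannot be said that the ratio will certainly be inflated. It does not dispose of the point. One recalibration sentence includes CVD illness, and it names the lab-based tool. The existing non-lab tool and the WHO charts are to be validated in their own right, and the new all-cause score does not cover them.

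A second reply is that all-cause death is also an endpoint and the Kaplan-Meier estimate is not tied to either. That is correct. Setting a CVD prediction against all-cause death would be a different mismatch, whose direction is not assured.

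Third, the protocol openly admits the missing non-fatal events and calls the data a pilot. The disclosure is fair, but the ratio is not adapted to it.

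A reader might also infer that treatment thresholds would then miss high-risk people, citing the 15% to 40% ten-year risks in the Economic Evaluation Model chapter. The documents do not support that. Those thresholds belong to an earlier cost-effectiveness analysis using the Framingham function, and no passage proposes scaling this tool to CVD deaths while still labelling it total CVD risk.

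**Conclusion.** The point holds as a defect of specification with a known direction. If the existing fatal-plus-non-fatal prediction is compared with observed CVD death, the ratio for an accurate tool is inflated by roughly 1/(fatal share). That is about 1.4 to 5 at matched five-year horizons for assumed shares of 0.7 to 0.2, and about 2.8 to 9.5 at R = 10% if the ten-year prediction is set against five-year observation.

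A reader might conclude that the plan is bound to make the tool look several-fold too high. The documents do not support that. They give no fatal share, the outcome mismatch alone reaches a factor of 3 only if about one third or fewer of predicted events are fatal, and a prediction re-anchored to CVD death would avoid it. The figures also rest on constant hazards and on an accurate tool.

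The effect is on absolute risk, hence on calibration. Discrimination need not be affected, and the cluster trial's endpoints are untouched.

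**What to change.** In Proposed Model Calibration Approach and Risk Prediction Validation, state one outcome and one horizon for both sides of the ratio:

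1. Assess calibration only for predicted CVD death against observed CVD death over the same years. Obtain the prediction by combining the NHEFS linear predictor with a CVD-death baseline hazard taken from the external national rates, so that the cohort is not used both to set and to test the level.
2. Report unmodified tools that predict fatal plus non-fatal CVD for discrimination only, with no predicted-to-observed ratio. Treat the WHO charts the same way if their outcome includes non-fatal events; the protocol should state what that outcome is.
3. Reconcile the ten-year prediction, the five-year observation and the five-year predicted risk.

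Hospital linkage is planned ("to permit linkage with the national mortality register and hospitalisation databases respectively"), but it is a weak basis for a total-CVD comparison. Folder numbers are collected only where available and the protocol says non-fatal events cannot be confirmed, so incomplete capture would leave the same upward bias. Any such analysis should be secondary and reported with its coverage.

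The cost is protocol wording and modest extra analysis, with no new visits or patients. The downside is that the calibration claim narrows to fatal CVD. Step 1 also assumes that the tool's relative effects carry over from all events to fatal ones, which should be stated.
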